#### Childhood overweight and obesity

The Copenhagen School Health Record Registry (CSHRR) includes every student attending a primary school in Copenhagen Municipality since birth in year 1930 through 1990 and comprises more than 370,000 records, which have been computerized for research purposes [22-24]. Overweight and obesity will be calculated from weight and height, which were measured at age 6–7 and at age 13–14 throughout the time period, but also annually until 1984. The CSHRR comprises approx. 10% of all Danes from each birth cohort. Birth weight, birth complications, gestational diabetes, pre-pregnancy weight and gestational and maternal age are retrievable from the National Medical Birth Registry. Data are available from 1973 onward.

#### T1D

The Danish Childhood Diabetes Registry covers all children age 0–15 at diagnosis with T1D. The registry covers all patients born since 1981 [25].

Currently a second phase of the project is planned. Finances are being applied for to also include outcomes such as type 2 diabetes (T2D), early cancer of the breast and colon, pre-eclampsia, dental diagnosis such a carries, psychiatric disorders such as schizophrenia, paranoid psychoses, mood disorders, organic mental disorders, and abuse of alcohol and other psychoactive substances. Information on development of these outcomes can be retrieved from the National Diabetes Registry, National Patient Registry, and the Danish Psychiatric Research Registry. In the future, a third phase will be planned and will examine association between additional exposure to vitamin D in fetal life and later development of other immunological disorders, including severe asthma, Crohn’s disease, inflammatory bowel diseases, and Juvenile idiopathic arthritis.

#### Vitamin D status (25(OH)D3)

Since May 1, 1981, routinely collected neonatal DBS samples taken by heel prick 48–72 hours after birth have been collected for all newborns in Denmark. After routine screening for congenital disorders, residual DBS cards are stored in the Biological Specimen Bank for Neonatal Screening at Statens Serum Institute [26]. Punches of stored surplus card samples will be used to measure neonatal 25(OH)D3 [27]. The assay detection method is a highly sensitive liquid chromatography tandem mass spectroscopy coupled with multiple reactant monitoring. Previous studies have shown that storage times of more than 20 years do not bias inter-individual variation in concentrations for a given birth cohort [28].

#### Education, unemployment, income and ethnicity

This information will be retrieved from the Statistics Denmark Fertility Database, which includes information on subjects of fertile age born since 1930 who still reside in Denmark. Social information is available for anyone born since 1981.

Data from the National Patient Registry, the CSHRR, The Danish Childhood Diabetes Registry, and the results of the DBS cards analyses will be merged and sent to Statistics Denmark for merging with their databases. Statistics Denmark will then create the relevant sub-datasets to be analyzed on-line.

### Exposure assessment

Four main analyses of exposure related to initiation and termination of vitamin D fortification will be considered for each of the disease outcomes:

1. perinatal exposure to vitamin D for offspring;

2. seasonal variation in vitamin D exposure in different pregnancy trimesters;

3. exposure to vitamin D adjusted for genetic and common environmental influences;

4. levels of vitamin D (25(OH)D3) measured in infant blood from DBS cards.

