**Methods/design:**

The study is based on the fact that in 1961 fortifying margarine with vitamin D became mandatory in Denmark and in 1972 low fat milk fortification was allowed. Apart from determining the influences of exposure prior to conception and during prenatal life, we will examine the importance of vitamin D exposure during specific seasons and trimesters, by comparing disease incidence among individuals born before and after fortification. The Danish National databases assure that there are a sufficient number of individuals to verify any vitamin D effects during different gestation phases. Additionally, a validated method will be used to determine neonatal vitamin D status using stored dried blood spots (DBS) from individuals who developed the aforementioned disease entities as adults and their time and gender-matched controls.

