### Objectives and hypothesis

The present study relies on a unique societal experiment in which all margarine and low fat milk products consumed by the Danish population were fortified with vitamin D, during two distinct time periods: in 1961–1985 fortifying margarine with vitamin D was mandatory in Denmark and in 1972–1976 low fat milk fortification was allowed. The present study also relies on the fact that in Danish national administrative and large research databases data can be linked at the individual level. This allows for the examination of the effects of exposure to additional vitamin D via fortified foods during fetal life in relation to later development of particular diseases. Initially the present study will include an in-depth examination of the influence of exposure to vitamin D during pregnancy for development of fractures of the wrist, forearm, upper arm and shoulder, as well as fractures of ankle; development of obesity; and development of T1D during child- and adulthood. Furthermore, the large number of subjects that will be followed will ensure that the effects of vitamin D exposure in relation to the timing of the seasons of gestational development also can be examined. Additionally, a validated method will be used to determine neonatal vitamin D status using stored dried blood spots (DBS) from individuals who develop the aforementioned disease entities as adults and their time and gender-matched controls. The main hypothesis is that low levels of vitamin D during critical phases of development have adverse effects on the long term risk of developing the above mentioned disease outcomes, and that exposure to extra vitamin D from food fortification has beneficial effects preventing the mentioned diseases.

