#### Perinatal exposure

Development of the disease outcomes will be compared for children born around the time when mandatory vitamin D fortification was initiated and terminated. The hypothesis is that individuals born 1–2 years after commencement of mandatory fortification (1961) and thus exposed to extra vitamin D during fetal development and for the next 24–25 years until 1985 (where fortification was ended), although unexposed thereafter, will have a lower lifetime risk of developing the aforementioned disease entities compared to individuals born 1 –2 years before fortification. Although also exposed to fortification for 24 – 25 years and unexposed thereafter, the latter group was unexposed during fetal life. Likewise, individuals born 1–2 years after mandatory fortification terminated in 1985, and who were unexposed to vitamin D both during fetal development and subsequently, will have a higher risk of later developing the diseases compared to those exposed during fetal life. Similar comparisons of disease development can be made in relation to higher exposure to vitamin D from 1972–1976, when fortified low fat milk was permitted.

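### For type 1 diabetes the named register can serve only the 1985 end of fortification and childhood onset, not the start, the milk period or adulthood, and that one contrast loses much precision once trend is adjusted for

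*Protocol article*

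**What the plan says.** Under Exposure assessment: "Four main analyses of exposure related to initiation and termination of vitamin D fortification will be considered for each of the disease outcomes". T1D is one of those outcomes.

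Objectives and hypothesis gives the periods: "in 1961–1985 fortifying margarine with vitamin D was mandatory in Denmark" and "in 1972–1976 low fat milk fortification was allowed". It sets the age range for this outcome as "development of T1D during child- and adulthood".

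Under Perinatal exposure, people born shortly after the 1961 start "will have a lower lifetime risk of developing the aforementioned disease entities compared to individuals born" shortly before it. People born after the 1985 end are predicted to have a higher risk than those exposed in fetal life. The section adds that similar comparisons are possible for the milk period.

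The T1D section under Databases names one source for this phase: "The Danish Childhood Diabetes Registry covers all children age 0–15 at diagnosis with T1D", and "The registry covers all patients born since 1981". The list of data to be merged (Education, unemployment, income and ethnicity) adds no other T1D source. The National Diabetes Registry appears only for second-phase outcomes, and the National Patient Registry is given fracture codes only.

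For the dried blood spot (DBS) study, the abstract takes samples "from individuals who developed the aforementioned disease entities as adults and their time and gender-matched controls"; the objectives say much the same.

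**The concern.** The stated scope for T1D is wider than the stated data. No analysis plan can supply cases that the only named register does not hold.

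Two safeguards that fractures and childhood obesity keep are lost for T1D:

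- **Opposite predictions.** Later births should have lower risk after 1961 and higher risk after 1985. A steady trend in one direction cannot produce both. T1D keeps only 1985, where a rising incidence would look like the hypothesised effect.
- **The sibling birth-order check.** It compares pairs in which the exposed sibling is the elder with pairs in which it is the younger. In T1D pairs spanning 1985 the sibling exposed in fetal life is always the elder.

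At stake is what a T1D result could show, and whether the precision suggested by Table 1 applies to it.

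**Working it through.** **1. Coverage of each switch by the T1D register (births from 1981, diagnosis at 0–15)**

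| Comparison | Births needed | In register? |
|---|---|---|
| Margarine start, 1961 | about 1959–1963 | No; register births begin 20 years later |
| Milk, 1972–1976 | early to late 1970s | No |
| Margarine end, 1985 | before and after 1985 | Yes; about four birth years before (1981–84) |
| Onset after age 15 | any | No |

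Two of the three T1D comparisons have no cases, nor do the sibling and season analyses built on them.

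**2. The plan's own figures.** Two proportions, pooled variance, two-sided α 0.05 (sidedness assumed), power 0.80, tabulated prevalence taken as the lower-risk group. At 0.5% and 50,000 per group, RR 1.266 gives p0 = 0.00500 and p1 = 0.00633. The null SE is √(2 × 0.005665 × 0.994335 / 50,000) = 0.000475 and the SE under the alternative is the same to three figures. (0.00133 − 1.96 × 0.000475) / 0.000475 = 0.84, which is power 0.80. Table 1 states 1.27. At 100,000 per group the solution is 1.185; Table 1 states 1.19. All ten cells agree when rounded up.

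**3. Trend alone at 1985.** The documents give no T1D trend, so 1–4% per birth year is an assumption. Births 1983–84 and 1986–87 have centres 3 years apart, so with no vitamin D effect RR = 1.01³ = 1.03 to 1.04³ = 1.12. In an unadjusted comparison (100,000 per group, 0.5%), the chance of a significant rise in the hypothesised direction is 7%, 16%, 30% and 48% for 1, 2, 3 and 4% per year, against a nominal 2.5%.

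**4. Cost of adjusting.** Poisson model with intercept, step at the switch and linear birth year, 1985 left out. Cases per birth year: λ = 50,000 × 0.005 = 250. With m cohorts per side, d the distance between the centres of the two sides, and S the sum of squares of birth year within sides:

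var(log RR) = 2/(mλ) + d²/(λS), where the second term is the cost of the trend term. Detectable RR = exp(2.80 × SE), with 2.80 = 1.96 + 0.84.

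- Two per side (m = 2, d = 3, S = 1). Unadjusted: 0.004, SE 0.063, RR 1.19. Adjusted: 0.004 + 9/250 = 0.040, SE 0.200, RR 1.75.
- Four per side (m = 4, d = 5, S = 10). Unadjusted: 0.002, SE 0.045, RR 1.13. Adjusted: 0.002 + 25/2,500 = 0.012, SE 0.110, RR 1.36.

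These take equal case counts on both sides. If counts after the switch are raised by the RR itself, the adjusted values fall:

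- Two per side at RR 1.63: 1/500 + 1/815 + 9/(125 × 2.63) = 0.0306, SE 0.175, RR 1.63.
- Four per side at RR 1.33: 1/1,000 + 1/1,330 + 25/(1,250 × 2.33) = 0.0103, SE 0.102, RR 1.33.

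The ranges are therefore about 1.6–1.75 and 1.33–1.36.

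**5. Lower prevalence.** The documents give no T1D risk to age 15. At an assumed 0.3% (λ = 150, equal counts), the adjusted values are 2.06 (two per side: 2/300 + 9/150 = 0.0667) and 1.49 (four per side: 2/600 + 25/1,500 = 0.020).

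**The case against.** Several points on the other side have force.

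- **Trend is not ignored.** Statistical analyses promises adjustment for secular trends, and the Discussion relies on adjacent birth years. A reader might infer that the T1D contrast is left open to trend bias. The documents do not support that: they promise an adjustment and do not say that T1D incidence is rising. What stands is that the adjustment is unspecified and costly with one switch.
- **Not all T1D analyses are exposed to trend.** DBS controls are matched on exact birth date, and the season contrasts are largely within a year. DBS cards begin in May 1981, so they fit the register's births well. It would be wrong to infer that T1D cannot be studied at all.
- **Table 1 is not wrong.** A reader might set lower T1D risks against 1.27 and 1.19 as a correction. Those figures are right for 0.5%. They simply carry no trend term and no lower prevalence.
- **The two switches are not described as a trend control.** The article gives them as hypotheses. That they would separate an effect from a steady trend follows from the predicted signs, not from a stated design purpose.
- **The adult wording is partly loose drafting.** The working sections speak of incident cases without an adult restriction, and the milk comparisons are only called possible.

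None of this supplies T1D cases born before 1981 or diagnosed after 15.

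**Conclusion.** The scope stated for T1D is wrong as written. With the source named, only the 1985 termination and onset at 0–15 can be studied, and the sibling birth-order check is unavailable. This follows from the text and needs no assumption.

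The loss of precision rests on the article's 0.5% prevalence and 50,000 births per year, a linear trend and 1985 omitted as wash-out. It takes the detectable RR from about 1.19 to 1.6–1.75, or from about 1.13 to 1.33–1.36. The Discussion's confidence that even minor effects are detectable does not carry over to the trend-adjusted T1D contrast. The size of any trend, and any prevalence below 0.5%, are assumptions.

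Obesity is touched only in wording. Its register covers births 1930–1990 and so spans every switch, but its measurements end at age 13–14.

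**What to change.** 1. In Objectives and hypothesis, Exposure assessment and Perinatal exposure, limit the T1D cohort, season and sibling analyses to the 1985 termination, births from 1981 and diagnoses at 0–15. State that the sibling birth-order check does not apply to T1D.
2. Keep the T1D season analysis around 1985 and the DBS analysis matched on exact birth date.
3. In the abstract and the objectives, replace the adult description of the DBS cases with the ages that the registers cover: T1D 0–15, obesity to 13–14.
4. Under Power calculation, state that Table 1 does not apply to the trend-adjusted T1D contrast. Give its detectable RR with the trend term, at 0.5% and, as a labelled assumption, at lower prevalences.
5. If the 1961 or 1972–76 T1D contrasts are to stay, name a source covering those births. The National Patient Registry would not by itself do. Its classified diagnoses start in 1977, when births of 1959–63 were about 14–18, and outpatient care is captured only after 1994, so it cannot separate incident from prevalent cases.

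Items 1 to 4 cost wording and one short calculation, with no new data. Item 5 is optional and needs a further register and a T1D case definition.

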#### Perinatal exposure

Development of the disease outcomes will be compared for children born around the time when mandatory vitamin D fortification was initiated and terminated. The hypothesis is that individuals born 1–2 years after commencement of mandatory fortification (1961) and thus exposed to extra vitamin D during fetal development and for the next 24–25 years until 1985 (where fortification was ended), although unexposed thereafter, will have a lower lifetime risk of developing the aforementioned disease entities compared to individuals born 1 –2 years before fortification. Although also exposed to fortification for 24 – 25 years and unexposed thereafter, the latter group was unexposed during fetal life. Likewise, individuals born 1–2 years after mandatory fortification terminated in 1985, and who were unexposed to vitamin D both during fetal development and subsequently, will have a higher risk of later developing the diseases compared to those exposed during fetal life. Similar comparisons of disease development can be made in relation to higher exposure to vitamin D from 1972–1976, when fortified low fat milk was permitted.

#### Seasonal variation in vitamin D exposure

The extra vitamin D from fortification is expected to be of particular relevance when stores are low [9]. To study seasonal variations, large datasets are needed and will be created by including individuals from 2–4 birth cohorts born before and after fortification. Whether or not exposure to vitamin D fortification in different gestational trimesters is important will be examined. For instance, influence of low vitamin D on obesity and adipose tissues may be particularly important for children whose third gestation periods occur during winter, while influence of low vitamin D on autoimmune diseases may be particularly important for children whose first gestational trimester occurs during winter.

#### Common environment and genetics adjusted exposure

To supplement the above mentioned cohort analyses, a nested sibling pair analysis, with one sibling identified before fortification was initiated (or terminated) and a gender-matched sibling identified after, will be applied for each of the analyses specified above. This design takes into account the common environment and genetics by matching on maternal genes and (assuming no change of partner) paternal genes. The genotypes of the two siblings may still differ, but on average with considerably less differences than between two unrelated subjects. This design assumes lack of birth order effects, but this can be partially tested by comparing results in sib-pairs in which the 1^st^ or 2^nd^ is the exposed dependent on whether they were born before, during or after the fortification period. The comparability of early life experiences in each sibling pair may reduce unmeasured confounding.

#### 25(OH)D3 level from DBS cards

Because the 25(OH)D3 levels in the newborn blood reflects the vitamin D status of the newborn as well as the mother at the end of pregnancy [29], measurement of 25(OH)D3 levels in DBS will serve as validation for the effect of fortification for incident cases. A control, matched for gender, exact date of birth, gestational age, being alive and with none of the aforementioned diseases will be selected and 25(OH)D3 measured. Date of birth matching criterion means that degradation of 25(OH)D3 is unlikely to bias results.

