Food disappearance statistics show that margarine intake decreased and low fat milk slightly increased during the period covered. Nevertheless, changes of this nature are not expected to influence results, because the intervention group and the control group will have been born in adjacent years. Moreover, any societal changes succeeding the initiation of mandatory fortification in 1961 or its termination in 1985 may influence the intervention and control groups similarly. Thus, we find it unlikely that changes in occurrence in the outcomes associated with the introduction and cessation of fortification will lead to spurious conclusions.

We do not collect any individual data on vitamin D intake. In contrary, the individuals in the database are unselected in relation to vitamin D exposure as well as to later disease occurrence. While assuming no ecological fallacies, this in fact may be considered a very strong feature of the present study. Neither confounding from external or internal factors, nor the lack of individual data on vitamin D intake, is a prerequisite for the study, as the influences of lifestyle differences (e.g. use of infant formula, individual diet intake, use of supplements) or societal changes (e.g. in breast feeding, fortified infant formulas, sun exposure) are independent of the vitamin D intervention.

We acknowledge, however, that the differences in prenatal exposure by any subsequent age imply a more simple difference in duration of exposure. Therefore, we will conduct robustness analyses where the age scale is adjusted so that the duration of exposure becomes the same and the difference then only whether the exposure was commenced/ended prenatal or postnatal.

Moreover, there might be regional and urban/rural differences in vitamin D intake. As information on individual’s place of residence is available from Statistics Denmark, it will be included into analyses.

As diet is usually different between families with higher socioeconomic status and those with lower status [31], maternal socioeconomic status may have affected margarine/milk intake and thus exposure to vitamin D. Information on socioeconomic position, education and ethnicity is available from Statistics Denmark and can be controlled for. Adjustments will also be made for maternal age, parity, gestational age and birth weight, which is information available from the birth and patient registries and Statistics Denmark (since 1973, 1977 & 1980, respectively).

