Finally, the uncertainties related to lack of knowledge about real vitamin D status in mother and offspring may be eliminated by assessing the measurement of infant blood vitamin D levels in those developing the three disease entities and comparing to time and gender-matched controls to examine actual exposure differences at birth.

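### The date-matched blood-spot comparison cannot validate the effect of fortification; it tests only whether neonatal 25(OH)D3 is associated with disease

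*Protocol article*

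**What the plan says.** All references are to the protocol article.

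- **Purpose.** The section on 25(OH)D3 level from DBS cards states that "measurement of 25(OH)D3 levels in DBS will serve as validation for the effect of fortification for incident cases".
- **Control selection.** The same section continues: "A control, matched for gender, exact date of birth, gestational age, being alive and with none of the aforementioned diseases will be selected". The reason given is storage: "Date of birth matching criterion means that degradation of 25(OH)D3 is unlikely to bias results".
- **How fortification is assigned.** Under Perinatal exposure: "Development of the disease outcomes will be compared for children born around the time when mandatory vitamin D fortification was initiated and terminated". Under Objectives and hypothesis: "in 1961–1985 fortifying margarine with vitamin D was mandatory in Denmark".
- **Individual intake.** Under Strengths and limitations: "We do not collect any individual data on vitamin D intake".
- **When cards exist.** Under Vitamin D status: "Since May 1, 1981, routinely collected neonatal DBS samples taken by heel prick 48–72 hours after birth have been collected for all newborns in Denmark". That section supports stability over long storage only for differences between people within one birth cohort.
- **What is planned and powered.** Statistical analyses describes the blood-spot comparison as people with the outcome against people without it. Table 2 gives the least detectable OR or HR of disease per 1 SD of 25(OH)D3.
- **The claim repeated.** The last paragraph of Strengths and limitations says that "the uncertainties related to lack of knowledge about real vitamin D status in mother and offspring may be eliminated", and ties this to the comparison of cases with time- and gender-matched controls.

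**The concern.** The study's argument has two links: fortification raised fetal vitamin D, and fetal vitamin D affects later disease. The blood spots are the only individual vitamin D measurement in the study, and the article relies on them to support the first link. The matching rule removes the contrast that this would need.

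The first link is a real question. Strengths and limitations says that fortification supplied only 15% of vitamin D intake on average. If it stays untested, a small or absent cohort effect could mean that fortification changed fetal vitamin D too little, or that fetal vitamin D does not matter for the outcome. The article tells readers that this uncertainty may be removed, and the plan as written does not do that.

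**Working it through.** **1. What the blood-spot sample was sized for.** Inputs from Power calculation: 1,000 cases, 1,000 controls, α = 0.05 (taken as two-sided), power 0.80, so the sum of the normal quantiles is 1.96 + 0.84 = 2.80. R² is the share of exposure variance explained by covariates.

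- OR = exp[2.80 / √(2000 × 0.25 × (1 − R²))]
- HR = exp[2.80 / √(1000 × (1 − R²))]

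| R² | OR computed | OR in Table 2 | HR computed | HR in Table 2 |
|---|---|---|---|---|
| 0 | 1.133 | 1.13 | 1.093 | 1.09 |
| 0.30 | 1.162 | 1.16 | 1.112 | 1.11 |
| 0.60 | 1.219 | 1.22 | 1.150 | 1.15 |

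Table 2 reproduces. It powers the association of 25(OH)D3 with disease. No figure in the article concerns the effect of fortification on 25(OH)D3.

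**2. The contrast within a pair.** Let F = 1 if the gestation fell under fortification and 0 otherwise. F depends only on the calendar dates of the gestation. Birth date and gestational age together fix those dates, and both are matching factors. So F(case) − F(control) = 0 in every pair, and season is equal too. Mothers may have eaten different amounts of fortified margarine, but without intake data a within-pair difference in 25(OH)D3 cannot be attributed to fortification.

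**3. Check by simulation.** Assumed inputs: 1,000 date-matched pairs, 60 repeats, half the birth dates fortified, fortification raising 25(OH)D3 by 0, 0.15 or 0.5 SD, and a log OR of disease of 0 or −0.2 per SD.

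| Fortification effect (SD) | Log OR per SD | Mean within-pair difference (SD) | Before–after difference in controls (SD) |
|---|---|---|---|
| 0 | 0 | 0.002 | −0.007 |
| 0.15 | 0 | 0.000 | 0.147 |
| 0.5 | 0 | 0.001 | 0.504 |
| 0 | −0.2 | −0.200 | 0.011 |
| 0.15 | −0.2 | −0.212 | 0.157 |
| 0.5 | −0.2 | −0.211 | 0.482 |

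The matched difference follows the disease association and does not respond to the size of the fortification effect. The before–after difference among controls recovers that effect.

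**4. What a before–after comparison could detect.** With n₁ and n₂ controls born before and after the end of fortification, the detectable difference is 2.80 × √(1/n₁ + 1/n₂) SD. If all cards are assayed at about one time, storage time is close to a linear function of birth date. For births spread evenly over the window, with a fraction p on one side of the boundary, a linear storage term explains R² = 3p(1 − p) of the before–after indicator. The detectable difference is then multiplied by 1/√(1 − R²). For 400/600:

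- unadjusted: 2.80 × √(1/400 + 1/600) = 0.181 SD
- R² = 3 × 0.4 × 0.6 = 0.72, so the multiplier is 1/√0.28 = 1.89
- adjusted: 0.181 × 1.89 = 0.34 SD

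| Split of 1,000 controls (assumed) | Unadjusted (SD) | R² | With linear storage term (SD) |
|---|---|---|---|
| 500/500 | 0.177 | 0.75 | 0.35 |
| 400/600 | 0.181 | 0.72 | 0.34 |
| 200/800 | 0.221 | 0.48 | 0.31 |
| 100/900 | 0.295 | 0.27 | 0.35 |
| 50/950 | 0.406 | 0.14 | 0.44 |

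The article gives no split, so every row is an assumption.

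**5. Which policy changes the cards can reach.** Cards begin in May 1981. The 1961 start and the 1972–1976 milk period lie wholly before that date. Only the 1985 termination has cards on both sides.

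**The case against.** The strongest defence is that the article says measurement, not the matched comparison, will serve as validation. Exposure assessment also lists blood-spot levels among the analyses related to the start and end of fortification. A condensed article could leave a before–after use of the same assays to the full plan. This has some force: such a use is not excluded. But the last paragraph of Strengths and limitations ties the claim expressly to time-matched controls, and Statistical analyses describes only the diseased versus non-diseased contrast.

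A second defence is that validation may be meant loosely, as support for the vitamin D–disease link. The sentence names the effect of fortification, so this is not what it says.

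A reader might also infer more than the documents support:

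- **That the blood-spot analysis is invalid.** It is not. Date matching is deliberate and protects the 25(OH)D3–disease association from storage degradation.
- **That a null cohort result could not be interpreted.** The cohort contrast estimates the effect of the policy, which is the question posed under Implications. Only the mechanism would be unclear.
- **That the existing assays settle the first link at 0.18 SD.** That figure omits the storage-time term that the comparison needs.
- **That controls free of all the study diseases bias the odds ratios materially.** The size would depend on cumulative disease risks that the documents do not give for these cohorts, and Statistical analyses describes controls as free only of the outcome concerned. At most, the two descriptions need reconciling.

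The May 1981 start of the cards is openly stated. It limits the claim and is not a concealed defect.

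**Conclusion.** The concern holds for the stated purpose of the blood-spot analysis. Information on fortification in the matched comparison is zero by construction, whatever the sample size. This follows from the article's own matching rule, its assignment of exposure by birth date, and the absence of intake data; it needs no outside figure. The matched analysis keeps its value as a test of neonatal 25(OH)D3 against disease, and no cohort estimate changes.

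The before–after comparison that could supply validation is feasible for 1985 only, and its precision is limited. With 1,000 controls it detects about 0.18 to 0.41 SD unadjusted over the assumed splits, and about 0.31 to 0.44 SD with a linear storage-time term. The adjusted range assumes evenly spread births and assays run at about one time.

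**What to change.** 1. In the section on 25(OH)D3 level from DBS cards, state that the matched analysis tests the association of neonatal 25(OH)D3 with disease.
2. Add a separate comparison of 25(OH)D3 among the already assayed controls born before and after the 1985 end of fortification. Adjust for calendar month of birth, and state in advance how storage time is handled and how wide the birth window is.
3. In that section and in the last paragraph of Strengths and limitations, limit the validation claim to the 1985 termination. Say that the 1961 start and the 1972–1976 milk period cannot be checked with blood spots. Replace the statement that uncertainty may be eliminated with one that gives the expected precision.
4. Reconcile the two descriptions of which diseases a control must be free of.

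**Cost.** Wording and one added analysis, with no further assays for the comparison as described. The price is in precision: the storage evidence covers only variation within a birth cohort, and storage time is nearly collinear with before/after. A narrower birth window reduces the number of controls and does not remove that collinearity. Once the birth dates of the controls are known, the detectable difference should be recalculated. If it is too large to be useful, the article should say that the effect of fortification on neonatal 25(OH)D3 remains an assumption.
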